### Randomisation

After baseline assessment, the 20 clusters will be randomised using a 1:1 allocation ratio to either the intervention arm receiving the PDC/Baby Ubuntu programme or the control arm receiving enhanced usual care. Randomisation will be stratified by district. Restricted randomisation will be used to ensure balance on cluster size which was determined to be potentially prognostic of intervention outcomes. The characteristics included in the restriction (district, cluster size) will be adjusted for in the analysis. Allocation will be completed by the trial statistician, not otherwise involved in the conduct of the trial. The outcome assessment team will be blinded to the allocation status of trial participants.

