### Participant timeline

Table 1 outlines the schedule of enrolment, interventions and assessments. Primary and secondary outcomes will be assessed at two timepoints: baseline (T0), and 12 months later after randomisation (T1).

**Table 1 Tab1:** Schedule of enrolment, assessment and intervention delivery

	Trial Period				
	Enrolment		Post-randomisation		Close-out
**Timepoint**	T0			T1	

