**Assessment**					
Sociodemographic data	X				
Clinical characteristics	X				
Family health-related quality of life (PedsQL)	X			X	
Child participation (YC-PEM)	X			X	
Caregiver knowledge & confidence	X			X	
Caregiver psychological distress (SRQ)	X			X	
Caregiver experience of stigma (Affiliate Stigma Scale)	X			X	
Caregiver economic activity (time-use survey)	X			X	
Child survival (vital status)				X	
Child development (MDAT/GSED)	X			X	
Child function (PEDI-CAT)	X			X	
Child health (hospitalisations)				X	
Child anthropometric measurement (weight, height, OFC)	X			X	

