### Data analysis

The trial will adopt a superiority design, evaluating whether the PDC/Baby Ubuntu intervention is superior to enhanced usual care in improving primary and secondary outcomes. Analyses will follow intention-to-treat principles. Clusters will be analysed according to their original randomisation, regardless of coverage or other variables.

The full analysis set will consist of all randomised subjects analysed according to the study arm to which they were assigned. The primary analysis will focus on all children at risk of developmental disabilities and their caregivers, comparing those receiving the PDC/Baby Ubuntu programme to the control group. The secondary analysis will compare children with developmental disabilities and their caregivers who received Baby Ubuntu to children with developmental disabilities in the control group. Superiority will be demonstrated if there are statistically significant improvements in the intervention arm versus the control arm for the prespecified outcomes.

Because of the relatively small number of clusters (n ≤ 20), cluster-level analyses will be used to assess the overall effect of the intervention. Specifically, in crude analyses, cluster-level means for each outcome measure will be generated and compared using t-tests. Adjustment for district and cluster size will be done using the two-stage approach described by Hayes and Moulton [43].

In further prespecified exploratory analyses, we will also analyse data at the individual level using generalised linear models (with an appropriate link function depending on the type of data) with random effects to allow for clustering of individuals. As this is not a confirmatory study, we do not plan any formal adjustment for multiple testing. Missing data will be handled using complete case analysis as the primary approach. Multiple imputation methods may also be used as a sensitivity analysis if substantial missing data exists (> 10% missing).

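### Both primary outcomes are measured before randomisation, but the named adjustment set is district and cluster size, so precision and protection from chance baseline imbalance are given up with 20 clusters

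*Protocol article*

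**What the plan says.** All references are to the protocol article.

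- **Timing.** Under Participant timeline: "Primary and secondary outcomes will be assessed at two timepoints: baseline (T0), and 12 months later after randomisation (T1". Table 1 marks PedsQL and YC-PEM at both points. Under Randomisation: "After baseline assessment, the 20 clusters will be randomised using a 1:1 allocation ratio". The T0 scores are therefore pre-randomisation covariates.
- **Balance by design.** Allocation is stratified by district. Beyond that, "Restricted randomisation will be used to ensure balance on cluster size". Baseline outcome is not a restriction factor.
- **Crude analysis.** Under Data analysis: "cluster-level means for each outcome measure will be generated and compared using t-tests".
- **Adjusted analysis.** In the same section: "Adjustment for district and cluster size will be done using the two-stage approach". The Randomisation section names the same two factors as the ones to be adjusted for.
- **Elsewhere.** The exploratory individual-level models list no covariates, and no section mentions a change score or a T0 covariate.

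**The concern.** The article chooses cluster-level methods because there are few clusters. With 10 per arm, most of the variance of the treatment comparison comes from differences between clusters, which recruiting more children hardly reduces. A covariate that predicts those differences can reduce it, and the T0 value of the same score is the natural candidate. It is already planned for every participant.

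Two things are at stake. One is precision, meaning a smaller detectable difference from the same data. The other is protection if the arms happen to start apart on quality of life or participation, since nothing in the design balances those scores.

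**Working it through.** **Inputs.** From Sample size and Table 2: 10 clusters per arm, 28 analysed per cluster (the sub-population with disabilities), PedsQL SD 20, YC-PEM SD 7.5, planning ICC 0.1, 80% power, 5% significance. The primary analysis covers all at-risk children: about 1,400 recruited over 20 clusters is 70 per cluster, or 56 if the same 20% loss applies. Assumed, because the article does not give them: the same SD and ICC at T0 as at endline, and all baseline-endline correlations.

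**1. The article's own figure.** Detectable difference = (1.960 + 0.842) × √(2 × SD² × [1 + (m − 1) × ICC] / ((c − 1) × m)), where c − 1 is the small-sample correction.
- PedsQL, m = 28: 2.802 × √(800 × 3.7 / 252) = 9.60. Table 2 has 9.6.
- YC-PEM, m = 28: 3.60. Table 2 has 3.6.
- PedsQL, m = 56: 2.802 × √(800 × 6.5 / 504) = 9.00.

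Table 2 reproduces with no baseline term, so the stated power neither uses nor needs the T0 scores.

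**2. Chance imbalance at baseline.** SD of the arm difference in mean T0 PedsQL = √(2 × 400 × (0.1 + 0.9/m) / 10).
- m = 28: √(80 × 0.1321) = 3.25 points, about a third of 9.6.
- m = 56: √(80 × 0.1161) = 3.05 points.

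Both ignore any reduction from stratification and restriction. The carry-over to endline is this gap times the slope: at a slope of 0.4, 3.25 × 0.4 = 1.3 points.

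**3. What stage-1 adjustment does.** Stage 1 applies one pooled slope b at both levels. With equal SD and ICC at the two times, b is about 0.1·rb + 0.9·rw, where rb and rw are the cluster-level and within-cluster correlations. The variance of a cluster mean is then

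V = 40 × (1 − 2b·rb + b²) + (360/m) × (1 − 2b·rw + b²),

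against 40 + 360/m unadjusted, which is 52.86 at m = 28 and 46.43 at m = 56.

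- rb = rw = 0.5: V is 0.75 of the unadjusted value. The PedsQL detectable difference falls from 9.60 to 8.32, equivalent to about 13 clusters per arm instead of 10.
- rb = 0.2, rw = 0.4: b = 0.38. At m = 28, V = 39.7 + 10.8 = 50.5, barely below 52.86.
- rb = 0, rw = 0.5: b = 0.45. At m = 28, V = 48.1 + 9.7 = 57.8, above 52.86. At m = 56, V = 48.1 + 4.8 = 52.9, above 46.43. The pooled slope adds noise between clusters, so power is lost.

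**4. Simulated power** for a difference of about 9.6 points at ICC 0.1, with T0 score adjusted at stage 1 and a t-test on cluster mean residuals at stage 2:

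| rb / rw | 28 per cluster (crude about 80%) | 56 per cluster (crude about 85%) |
|---|---|---|
| 0.4 / 0.4 | 86–87% | 91% |
| 0.6 / 0.5 | 92% | 96% |
| 0.7 / 0.6 | 96–97% | 98% |
| 0.2 / 0.4 | little gain | little gain |
| 0 / 0.3 to 0.5 | loss of about 1–3 points | loss of about 2–5 points |

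Type I error stayed near 5%. A stricter comparison, with 15 degrees of freedom and district and cluster size in both analyses, gives 82% to 89% for 0.4/0.4 at 56 per cluster.

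**The case against.** The strongest reply is that covariates are usually settled in the statistical analysis plan, which is not shown. The article nowhere says that district and cluster size are the only adjusters; it names them because they are the restriction factors. The two-stage method can also accept individual covariates. A fuller plan may therefore already include the T0 score. What weakens this reply is that the article does state an adjustment set, twice and identically, and an analysis plan that follows it would leave the T0 score out.

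The second reply is that the gain depends on correlations nobody has reported. This stands. Newborns are eligible and endline is 12 months later, so prediction may be weak for the youngest children, and step 3 shows that the method can lose power.

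A reader might also infer more than the documents support:

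- **That the planned analysis is biased or underpowered.** It is neither. It is unbiased over randomisations, the t-test's standard error already reflects chance imbalance, and Table 2 holds without a baseline term.
- **That a baseline gap passes in full into the result.** Only the part given by the slope does.
- **That complete-case analysis is invalid without the T0 score.** The article does say "Missing data will be handled using complete case analysis as the primary approach", but it allows multiple imputation as a sensitivity analysis above 10% missing. Part of the planned 20% is non-consent, for whom no T0 score exists. Under an additive effect, loss that depends on baseline equally in both arms leaves the difference unbiased.
- **That child age must also be a covariate.** The article says the YC-PEM will be adapted and validated and gives no scoring from which an age effect could be judged.

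**Conclusion.** The point holds as a recommendation on efficiency and robustness. Nothing is stated wrongly, but a planned pre-randomisation measurement of each primary outcome goes unused in a trial with 20 clusters. If the cluster-level correlation is 0.4 or more, the gain is worth having: roughly 6 to 17 points of power at 28 per cluster and 6 to 13 at 56. If it is near zero, the cost is up to about 5 points. These sizes assume ICC 0.1, equal SD and ICC at T0 and endline, and, for the 56-per-cluster figures, the same 20% loss among all at-risk children.

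**What to change.** State, before any endline data are analysed, that stage 1 of the adjusted two-stage analysis of each primary outcome includes the participant's T0 value of the same score alongside district and cluster size. Reduce the stage-2 degrees of freedom for the cluster-level covariates: two indicators for three districts plus cluster size gives 20 − 2 − 3 = 15. The individual T0 score costs none. Prespecify a simple imputation for a missing T0 value, and keep the crude t-test as supportive.

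Extend the adjustment only to secondary outcomes measured with the same instrument at T0 and T1. Mortality and hospitalisation are recorded at endline only. The developmental measure changes from GSED to MDAT with age, so children who pass age 3 may lack a matching score.

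The cost is wording and a few lines of code, with no new data, plus the modest power loss already described if cluster-level correlation is near zero. The Trial status section reports endline assessments under way and no data analysed at submission; if that is still so, the change can be made as a prespecified one.

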### Data collection

Screening, informed consent and baseline/endline survey data collection will take place at health centres. Trained data collectors will collect survey data via structured interview with the child’s primary caregiver. Developmental progress will be assessed on direct assessment of the child using standardised, culturally-relevant developmental assessment tools. Data collectors will receive training for one week, including pilot for assessment and feedback. Pilot data will be used in the final analysis, dependent on data quality. All data collection tools will be translated into Kinyarwanda and back translated into English before finalisation. Data collection general procedures will be guided by a Standard Operating Protocol. Participants will be provided remuneration for participating in the baseline/endline survey and for transport (total 6,000 RWF).

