### Sample size

The primary analysis will be conducted amongst all children at risk of developmental disabilities and their caregivers. Secondary analysis will be conducted for the sub-population of children with developmental disabilities. Sample size calculations are based on the primary effectiveness outcomes amongst the sub-population of children with developmental disabilities, as this is the population for which data were available and is an important secondary analysis population. As a result, the trial will be powered to detect smaller intervention effects for the primary analysis population of all at risk children. We assume 10 clusters per trial arm with 35 children with developmental disabilities per cluster, for a total of 700 children with development disabilities overall, of whom 20% will not consent to participate in the evaluation or will be lost to follow-up. This results in a total of 560 children with developmental disabilities with outcome data (280 in each trial arm, 28 per cluster). Previously published data from a Ugandan cohort of children (< 3 years) with developmental disabilities suggest a mean family health-related quality of life score (PedsQL) of 60 amongst care as usual families (standard deviation 20) [28]. Data from Brazil suggest a mean YC-PEM home participation frequency raw score of 59 (standard deviation 7.5) and a mean YC-PEM home participation involvement raw score of 43 (standard deviation 7.5) in those receiving standard care [42]. Based on these values, Table 2 indicates detectable differences for family health-related quality of life and child participation among children with developmental disabilities, with 80% power and 5% significance level, for a range of intra-cluster correlation coefficient (ICC) scenarios. Detectable differences are shown as absolute difference, relative difference and as Cohen’s effect size.

**Table 2 Tab2:** Detectable differences in family health-related quality of life and child participation primary outcomes

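### The primary comparison uses complete cases with no baseline score, and multiple imputation stays optional above the plan's own 10% threshold, while the analysis set is described as all randomised subjects

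*Protocol article*

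**What the plan says.** All of the following comes from the protocol article.

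- **Analysis set (Data analysis).** "The full analysis set will consist of all randomised subjects analysed according to the study arm to which they were assigned". The Abstract describes the set in the same way. The section also states "Analyses will follow intention-to-treat principles" and ties this to analysing clusters as originally randomised.
- **Missing data (Data analysis).** "Missing data will be handled using complete case analysis as the primary approach". Then: "Multiple imputation methods may also be used as a sensitivity analysis if substantial missing data exists", where substantial means more than 10% missing.
- **Primary test (Data analysis, Randomisation).** Cluster means are compared by t-test. The two-stage cluster-level adjustment covers district and cluster size. No baseline outcome score is named, although Table 1 shows PedsQL and YC-PEM measured at both T0 and T1.
- **Expected attrition (Sample size).** The plan assumes "10 clusters per trial arm with 35 children with developmental disabilities per cluster", 700 in total, "of whom 20% will not consent to participate in the evaluation or will be lost to follow-up".
- **Discussion.** Loss to follow-up in this mainly rural population is named as a possible challenge.

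**The concern.** A child without endline scores is randomised but does not enter the complete-case cluster mean. The set that produces both primary results is therefore not the set that the plan names.

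An unadjusted mean of observed scores stands for the whole randomised cohort only if those lost would have scored like those kept, or if the discrepancy is the same in both arms. Differential loss is plausible here. Participants are not blinded, intervention families have a programme to stay engaged with, and control families receive a printed handout. Nothing in the primary comparison would correct loss related to baseline status, although the baseline scores needed to do so are collected.

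The plan sets its own threshold for substantial missingness but requires nothing when it is crossed. Whether to impute would then be decided once the amount and pattern of missing data are known. The primary method, the threshold and the optional wording are all fixed in the article, so this is not a detail left to an analysis plan.

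**Working it through.** **1. The plan's own figures.** 700 × (1 − 0.20) = 560 children, and 35 × 0.8 = 28 per cluster, as stated. The detectable PedsQL difference with SD 20, m = 28 per cluster, c = 10 clusters per arm and ICC 0.1 is

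(1.96 + 0.84) × SD × √{2[1 + (m − 1)ICC] / [m(c − 1)]} = 2.80 × 20 × √{2 × 3.7 / 252} = 9.60,

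which reproduces the stated 9.6. The same formula gives 7.65 and 5.63 at ICC 0.05 and 0.01, against 7.7 and 5.6 in Table 2.

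**2. How much of the 20% can be missing endline data.** Consent is taken at recruitment and clusters are randomised after baseline, so a family that refuses at recruitment is never randomised. If a share q refuses, the missing share among enrolled children is 1 − 0.8/(1 − q):

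| Assumed non-consent q | Missing among enrolled |
|---|---|
| 0% | 20.0% |
| 5% | 15.8% |
| 10% | 11.1% |
| 11.1% | 10.0% |
| 15% | 5.9% |
| 20% | 0% |

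The 10% threshold is passed when q < 1 − 0.8/0.9 = 11.1%, that is, fewer than 78 refusals among 700. The document does not give q.

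**3. Size of the bias, by formula.** Let f be the fraction missing in an arm and D the mean of observed minus the mean of missing scores. The bias of the complete-case difference (intervention minus control) is f_I·D_I − f_C·D_C. All values of f and D below are assumptions.

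| f_I, f_C | D_I, D_C | Bias (PedsQL points) |
|---|---|---|
| 20%, 20% | 10, 10 | 0 |
| 20%, 20% | 0, 10 | −2.0 |
| 20%, 20% | 10, 0 | +2.0 |
| 15%, 25% | 10, 10 | 1.5 − 2.5 = −1.0 |
| 15%, 25% | 5, 5 | 0.75 − 1.25 = −0.5 |

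**4. Size of the bias, by simulation.** The set-up was 20 clusters of 70 (1,400/20), SD 20, ICC 0.1 and no true effect. Loss depended on the baseline score (log-odds 0.7 to 1.0 per SD in absolute value), and the baseline–endline correlation was 0.4 to 0.6. SD and ICC come from the Sample size section; the loss model and the correlation are assumed.

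| Loss, control / intervention | Selection on baseline | Bias, absolute | False-positive rate |
|---|---|---|---|
| 25% / 15% | control arm only | about 1 to 2.3 | about 5.5–12% |
| 25% / 15% | same in both arms | about 0.6–0.8 | about 5.3–6.2% |
| equal | same in both arms | 0 | about 5% |

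The sign follows who is lost: losing low-scoring control families works against the intervention, and losing high-scoring ones favours it. At 12% / 8% loss, one run gave about 0.95 points.

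**5. Remedies in the control-only scenario.** Imputation by arm with cluster and baseline score left a bias within 0.2 points and a rejection rate of 3.4–5.2%. Staying with complete cases but putting the baseline score in the first stage of the two-stage adjustment left at most 0.13 points and a rejection rate of 4.2–5.4%.

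**The case against.** **The 20% is not a loss figure.** A reader might infer that the plan expects loss at double its own threshold. The text does not support that. The 20% combines non-consent with loss, is stated for the sub-population with disabilities, and some or all of the non-consent precedes randomisation. This stands, so only up to 20% can be said. Two features point the other way without settling it: Table 1 marks consent again at T1, and the plan speaks of recruiting about 1,400 children including the 700.

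**Intention-to-treat is not abandoned.** A reader might also infer a breach of intention-to-treat. The article links that principle to analysis by assigned arm, which is kept. The conflict is only with the all-randomised description of the set.

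**The scenario is chosen.** No passage supports 25% against 15% loss, or selection in one arm only. This stands: bias is possible, not shown, and milder assumptions shrink it or remove it.

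**Complete-case analysis as such is not the cause.** In the simulated scenario, adding the baseline score to the first stage removes the bias without imputation. This stands and widens the choice of remedy. Imputation also succeeds there partly by construction, since loss depended only on a variable in the imputation model.

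**Problems would be visible anyway.** Dissemination commits to CONSORT with its cluster extension, and individual-level random-effects models are planned. Reporting would show loss by arm but would not correct for it. The models are exploratory and are not stated to include baseline scores.

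**Pilot data and deaths.** The sentence "Pilot data will be used in the final analysis, dependent on data quality" might suggest exclusions after randomisation, but the pilot is described within data-collector training and nothing places the decision after allocation. Nor does anything say that scores would be imputed for children who died; that detail belongs in an analysis plan. Neither is part of this point.

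**Conclusion.** The point holds in limited form. The plan names one analysis set and analyses another. Its primary comparison has no protection against baseline-dependent loss that differs by arm, and its only stated safeguard is optional even above its own threshold.

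Against the stated detectable difference of 9.6 points, the control-only scenario gives 1/9.6 = 10% to 2.3/9.6 = 24%. The same selection in both arms with unequal loss gives 0.6/9.6 = 6% to 0.8/9.6 = 8%. Equal, equally selective loss gives nothing. The 9.6 refers to the disability sub-population at 28 per cluster. For all at-risk children, if the same 20%, SD and ICC applied (56 per cluster), the formula in step 1 gives 9.0, so the shares would be slightly larger.

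These sizes rest on assumed loss rates, selection strength and baseline–endline correlation. Both remedies deal with loss that depends on baseline status; neither was tested against loss driven by the unseen endline score.

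**What to change.** 1. In Data analysis, change *may* to *will*: whenever more than 10% of endline primary scores are missing, report multiple imputation beside the complete-case result. Impute by arm, with cluster and the baseline outcome score in the model, and follow with the same two-stage cluster-level test. An equally simple way to remove bias from baseline-dependent loss is to add the baseline outcome score to the first stage of the two-stage adjustment.
2. Describe the primary analysed set as randomised participants with endline data, analysed by assigned arm, and not as all randomised subjects. Align the Abstract.

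The cost is wording and some extra analysis on variables already collected at T0, with no added participants or visits. The downside is reliance on an imputation model and one more result to report. Trial status says that no data had been analysed at submission; the commitment should be dated before analysis starts.
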